**Fig 1 pone.0316811.g001:**
[figure not shown]
Schedule of enrolment, interventions, and assessments.

**Fig 2 pone.0316811.g002:**
[figure not shown]
Simplified schematic of the trial design.

### Intervention

Subjects will be randomly assigned 1:1 to the ceftriaxone intervention group or the control group after signing informed consent on a computer-generated randomization table generated by an investigator not involved in the clinical trial. Patients who meet the inclusion criteria will undergo endotracheal intubation routinely according to the operating specifications of our unit. Patients in the intervention group will be given 100mL 0.9% sodium chloride with 2g ceftriaxone sodium intravenously over the course of one hour within two hours after endotracheal intubation. Patients in the control group will receive 100 mL 0.9% sodium chloride injection intravenously over the course of one hour within two hours after endotracheal intubation. Other treatment measures after endotracheal intubation (ie: prevention of aspiration, withdrawal of mechanical ventilation) are the same as conventional treatment. Neither the investigators nor the patients will be aware of the group assignments during the study. Open label is allowed in case of serious adverse effects such as allergic reaction.

### Data collection

#### Patient characteristics

The general data of the patients will be collected, including gender, age, height, weight, BMI, comorbidities, Acute Physiology and Chronic Health Evaluation II (APACHE Ⅱ) score, Sequential Organ Failure Assessment (SOFA) score, history of medication allergy, diagnosis, smoking history, drinking history, bed rest history, chest radiograph or chest CT manifestations before endotracheal intubation, laboratory test results (white blood cell count, neutrophil ratio, C-reactive protein and procalcitonin), body temperature, cause of ICH, time of onset of aspiration pneumonia after enrollment, duration of mechanical ventilation, length of ICU stay, length of hospital stay, and 28-day survival.

#### Intubation characteristics

Intubation characteristics will be collected, including whether vomiting occurred before endotracheal intubation; whether obvious aspiration occurred before endotracheal intubation; whether aspiration occurred during endotracheal intubation; whether mechanically ventilated; endotracheal intubation time; endotracheal intubation type; whether analgesic and sedative drugs were used before intubation; whether intubation was difficult; whether repeated intubation attempts were necessary.

#### Antibiotic characteristics

Antibiotic characteristics will be collected, including time of administration, antibiotic type, dose, frequency, and days of antibiotic use after enrollment; sputum or broncho alveolar lavage fluid (BALF) culture results during endotracheal intubation and sputum or BALF culture results during aspiration pneumonia.

### Research outcomes

The primary outcome is the incidence of aspiration pneumonia within 48 hours after endotracheal intubation. Aspiration pneumonia is defined the presence of new or advanced infiltrating shadows, consolidation shadow, or ground glass shadow on chest X-ray or CT in patients without a diagnosis of community-acquired pneumonia, healthcare-associated pneumonia, or aspiration pneumonia, combined with two or more of the following clinical symptoms: (1) fever, body temperature >38°C; (2) purulent airway discharge; (3) white blood cell count >10 ×10 ^ 9 / L or<4×10^9/L. Secondary outcomes include: intensity of antimicrobial use, length of hospital stay, duration without mechanical ventilation, and 28-day mortality. A subgroup analysis will be conducted in patients with high and low aspiration pneumonia risk, which will be defined as follows: low-risk patients will exhibit none of the following intubation characteristics: visible stomach contents during intubation, aspiration suspected, and evidence of aspiration by bronchoscopy. High risk patients will exhibit one or more of the following intubation characteristics: visible stomach contents during intubation, aspiration suspected, and evidence of aspiration by bronchoscopy.

The intensity of antimicrobial use is defined as:

$\frac{\mathrm{Antimicrobial}\;\mathrm{consumption}\;(\mathrm{cumulative}\;\mathrm{DDD})}{\mathrm{Days}\;\mathrm{of}\;\mathrm{patients}\;\mathrm{admitted}\;\mathrm{in}\;\mathrm{the}\;\mathrm{same}\;\mathrm{period}}\times 100$
where DDD is the defined daily dose.

The intensity of antibiotic use in a particular patient is defined as:

$\frac{\mathrm{Antimicrobial}\;\mathrm{consumption}\;(\mathrm{cumulative}\;\mathrm{DDD})}{\mathrm{Days}\;\mathrm{of}\;\mathrm{hospital}\;\mathrm{stay}}\times 100$

$\frac{\mathrm{Antimicrobial}\;\mathrm{drug}\;\mathrm{consumption}/DDD}{\mathrm{Days}\;\mathrm{of}\;\mathrm{hospital}\;\mathrm{stay}}\times 100$

$\frac{\mathrm{Single}\;\mathrm{dose}\;\mathrm{of}\;\mathrm{antibiotics}\times \mathrm{frequency}\;\mathrm{of}\;\mathrm{use}\times \mathrm{days}\;\mathrm{of}\;\mathrm{use}/\mathrm{DDD}}{\mathrm{Days}\;\mathrm{of}\;\mathrm{hospital}\;\mathrm{stay}}\times 100$

### Adverse event monitoring

Patients with a history of allergy to cephalosporins will be excluded to avoid allergic reactions to the drugs. Allergic reactions include high fever, rash, pruritus, dyspnea, laryngeal edema, and anaphylactic shock. Once allergy occurs, the drug will be stopped immediately, and epinephrine or appropriate first aid measures (e.g., airway management, intravenous rehydration, antihistamines, corticosteroids, vasoactive drugs) will be given to patients with severe acute hypersensitivity reaction according to clinical indications. Serious adverse reactions will be reported to the Ethics Committee immediately.

### Sample size calculation

A total of 50 patients will be included in the preliminary study, with 25 patients in each of the ceftriaxone and control groups. For the preliminary results, the incidence of pneumonia within 48 hours after endotracheal intubation in the two groups was 16%(4/25) and 32%(8/25), respectively. The sample size estimation formula for the comparison of two sample rates will be used to estimate the sample size; the test level α was set at 0.05, and the type Ⅱ error probability β was set at 0.2. The patients will be included according to 1:1 randomization, and the required sample size of each group was calculated to be 177 cases by two-sided test. Considering the loss of follow-up, based on the loss rate of 10%, at least 197 cases subjects were needed in the each group.

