### Trial status

At the time of manuscript submission, the study is in the preparation phase for recruitment. This is the first version of the protocol completed on September 30, 2022. Recruitment is scheduled to begin in April 2023 and expected to be completed by April 2025.

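### The stated 177 per group does not follow from the stated inputs (16% vs 32%, two-sided 5%, 80% power), which give 108 to 123; at 177 the power is about 93–95%

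*Protocol article*

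**What the plan says.** All the inputs stand in one paragraph of the protocol article, under Sample size calculation. The preliminary incidence of pneumonia within 48 hours "in the two groups was 16%(4/25) and 32%(8/25), respectively", with the ceftriaxone group listed first. On the error rates, "the test level α was set at 0.05" and "the type Ⅱ error probability β was set at 0.2". On allocation, "The patients will be included according to 1:1 randomization". The method is described only as the formula for comparing two rates, with no variant named. The result is that "the required sample size of each group was calculated to be 177 cases by two-sided test", raised to at least 197 per group for a 10% loss rate.

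The Statistical analysis section compares the primary outcome with a chi-square or Fisher's exact test. The article gives no other target difference, power, multiplicity adjustment or margin for the primary outcome.

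**The concern.** A reader who puts the printed inputs into any common two-proportion formula gets a number well below 177. At least one of the rates, alpha, beta or the 177 is therefore misreported, and the reader cannot tell which.

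This matters for two reasons. First, the sample size statement tells readers which difference the trial was built to detect. A null result means one thing if the trial had 80% power for a 16-point difference and another if it had about 94%. Second, the figure sets how many patients are randomised: 394 in total as stated, against 240 to 274 from the printed inputs. An ethics committee or a reader cannot verify that number as written.

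**Working it through.** **Inputs** (all from Sample size calculation): p1 = 0.16, p2 = 0.32, difference d = 0.16, two-sided alpha 0.05 (z = 1.960), power 0.80 (z = 0.842), 1:1 allocation. Hence (1.960 + 0.842)² = 7.849. The mean rate is 0.24. The unpooled variance sum is 0.16×0.84 + 0.32×0.68 = 0.352, the pooled one is 2×0.24×0.76 = 0.3648, and d² = 0.0256.

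**Trying to reproduce 177 per group**

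- Unpooled: 7.849 × 0.352 / 0.0256 = 107.9, so 108.
- Arcsine: 2 × 7.849 / h², with h = 2·arcsin√0.32 − 2·arcsin√0.16, gives 109.0, so 109.
- Pooled under the null, unpooled under the alternative (Fleiss): (1.960·√0.3648 + 0.842·√0.352)² / 0.0256 = 110.7, so 111.
- Simple pooled: 7.849 × 0.3648 / 0.0256 = 111.8, so 112.
- Fleiss with continuity correction: (110.7/4) × [1 + √(1 + 4/(110.7×0.16))]² = 122.8, so 123.
- Exact power of Fisher's test, the more conservative of the two planned tests: 79.7% at 120 per group and 80.5% at 123.

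The choice of formula moves the answer by 15 patients per group (108 to 123). The gap to the stated figure is at least 177 − 123 = 54. In ratio terms, 177/123 = 1.44 and 177/108 = 1.64, an excess of 44–64%.

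**Changing one setting at a time, rates held at 16% vs 32%**

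- One-sided 5%, 80% power: 88, or 100 with continuity correction.
- Two-sided 5%, 90% power: 145 to 160.
- Two-sided 5%, 95% power: 183 (Fleiss) or 195 (continuity-corrected).
- Two-sided alpha 0.01, 80% power: 165 (Fleiss) or 178 (continuity-corrected).

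Only the last comes close to 177, and it contradicts the stated alpha.

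**Power at 177 evaluable per group, 16% vs 32%**

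- Normal approximation: (0.16·√177 − 1.960·√0.3648) / √0.352 = 1.59, so 94.4%.
- Exact, chi-square test: 94.7%.
- Exact, Fisher's test: 93.2%.

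The type II error at the stated size is therefore about 0.05 to 0.07, not 0.2. If no patients were lost and all 197 per group were evaluable, power would be 96.3% (normal approximation).

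**The loss step.** 177 / (1 − 0.10) = 196.7, so 197. This reproduces. The same step turns 108 and 123 into 120 and 137 per group, or 240 and 274 in total.

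**What 177 would detect with a 32% control rate** (normal approximation): 80.4% power against 19% and 73% against 20%.

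**The case against.** **The error is in the safe direction.** The trial is larger than its own assumptions require, so it is not underpowered under them. Allocation, the primary test and its type I error are unaffected. This stands, and it lowers the severity. A larger trial can also be defended: the preliminary difference rests on 25 patients per arm, with a 95% Newcombe interval of about −8 to +38 percentage points. That justifies keeping the size. It does not make the printed inputs and result agree.

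**An unseen document might explain the figure.** This does not stand. The article prints every input as well as the result, and they disagree as printed.

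**A reader might infer that the real design effect was 32% vs 19%.** The document does not support this. Several unstated input sets give about 177: 19% vs 32% at 80% power (176), 16% vs about 28.5% (173), two-sided alpha 0.025 with 90% power (177 by the simple pooled formula), and alpha 0.01 with continuity correction (178). None is declared, so 19% can illustrate power but cannot be presented as the sponsor's target.

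**A reader might also infer that the preliminary patients count towards the 394, which would threaten the type I error.** The wording invites this, since "A total of 50 patients will be included in the preliminary study" is in the future tense although results by arm follow. But those results were already available to set the size, and Trial status says that "the study is in the preparation phase for recruitment". Read together, these place the 50 patients before the trial, and nothing counts them in the 394. The future tense looks like loose drafting: the same paragraph says the formula will be used and then reports its result in the past tense. Silence in a condensed article does not support a pooling concern.

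**Conclusion.** The sample size statement is wrong as written. The stated rates, alpha, beta and allocation give 108 to 123 evaluable patients per group, not 177; and 177 per group gives about 93–95% power for 16% vs 32%, not 80%. The inflation to 197 is correct given 177, so the fault lies in the 177 or in an input that was misreported. Which of these it is cannot be settled from the article.

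The conclusion assumes a superiority comparison of two independent proportions, as the article describes, with no unreported adjustment to alpha or power. It does not depend on the choice among the standard formulas.

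This should be fixed, but it is not critical: the discrepancy is towards a larger trial and changes neither the planned test nor enrolment.

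**What to change.** Keep 197 per group and correct the paragraph in one of two ways:

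- If another rate, alpha, power or formula produced 177, state it.
- Otherwise, restate the power: 177 evaluable patients per group give about 94% power for 32% vs 16% at two-sided 5%. To show sensitivity, add that power is about 80% for 32% vs 19% and 73% for 32% vs 20%, labelled as illustrations and not as the design effect.

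Keeping 197 is a recommendation that the article's own figures do not compel. It rests on how imprecise the preliminary difference is, which also argues against cutting the trial to 108–123 evaluable per group. The cost is one corrected paragraph, with no change to enrolment, allocation or analysis.

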### Statistical analysis

SPSS 20.0 will be used for statistical analysis. Demographic factors and baseline characteristics, such as age, sex, APACHE II score, and SOFA score, will be adjusted for using appropriate statistical methods. These adjustments may include logistic regression for binary outcomes or stratified analysis if needed. The primary outcome, which is the incidence of aspiration pneumonia within 48 hours of intubation, will be compared between the control and intervention groups using either the chi-square test or Fisher’s exact test, depending on the distribution of the categorical data. For the secondary outcomes, continuous variables like length of ICU stay, duration of mechanical ventilation, and hospital length of stay will be described using mean ± standard deviation or median (interquartile range) depending on the distribution of the data. Differences between the groups will be tested using independent t-tests for normally distributed data or Mann-Whitney U tests for non-normally distributed data. Categorical outcomes such as 28-day mortality will be analyzed using chi-square or Fisher’s exact test. For any time-to-event outcomes, such as the time until the development of aspiration pneumonia or extubation, Kaplan-Meier survival analysis will be used, with differences between the groups assessed via the log-rank test.

In terms of assumptions, the study will check for normality and independence in the data, particularly for tests like the t-test or chi-square test. If assumptions of normality are violated, appropriate data transformations (e.g., logarithmic transformation) or non-parametric tests will be used. For categorical data, Fisher’s exact test will be used if expected cell counts are less than 5 in any of the categories. Missing data will be handled using a complete case analysis, where possible. If missing data is substantial, multiple imputation techniques will be applied to ensure the integrity and reliability of the analysis.

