In a study evaluating the risk factors for pneumonia within 48 hours after intubation, Rello et al. [23] found that patients with respiratory/cardiac arrest and coma had the highest incidence of pneumonia in the first 48 hours. Antibiotic use during this period reduced the incidence of pneumonia, while other preventive measures such as subglottic suction were ineffective. Sirvent et al. [24] conducted a randomized trial to evaluate the effectiveness of two doses of cefuroxime administered within 24 hours after intubation in reducing the incidence of early-onset ventilator-associated pneumonia (VAP) in patients with closed head injury (Glasgow Coma Scale score < 12). A retrospective cohort study by Vlad Dragan et al. [25] reached a different conclusion, finding instead that prophylactic antimicrobial therapy in patients with acute aspiration pneumonia does not provide clinical benefit, has no effect on mortality improvement, and may generate antibiotic selection pressure and increase the number of days of subsequent antibiotic treatment. In these cases, however, antibiotic use may be more akin to short-term treatment than true prevention, and long-term antibiotic use may increase the risk of subsequent infection by resistant microorganisms. For this reason, we decided to use a single dose of ceftriaxone, an antibiotic which has a long half-life and is effective against the main pathogens responsible for most endotracheal intubation-induced aspiration pneumonia.

A previous similar study by Valles et al. [26] showed that a single dose of antibiotics significantly reduced the incidence of VAP in mechanically ventilated comatose patients. It also reduced mechanical ventilation and ICU length of stay, and had no effect on mortality or the incidence of multidrug-resistant microbial infections. However, this was a non-randomized study, and there was bias in the selection of patients in the control group. The incidence of chronic obstructive pulmonary disease in the control group was higher, which resulted in a greater degree of airway pathogen colonization before intubation, and more patients requiring neurosurgical intervention were included in the control group. Our study will be randomized, making it a more effective analysis of a single antibiotic dose as a prophylactic measure for aspiration pneumonia.

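### Covariate adjustment is promised with an open list and optional methods, but the primary outcome is tested unadjusted and the adjusted result has no stated role

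*Protocol article*

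**What the plan says.** Three consecutive statements in the Statistical analysis section bear on the point.

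1. Demographic and baseline factors will be adjusted for. Age, sex, APACHE II and SOFA are given as examples (*such as*), and no outcome is named.
2. On the method: "These adjustments may include logistic regression for binary outcomes or stratified analysis if needed".
3. The incidence of aspiration pneumonia within 48 hours, the primary outcome, "will be compared between the control and intervention groups using either the chi-square test" or Fisher's exact test. The same section gives the rule for choosing between them (expected cell counts below 5).

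The Sample size calculation section sizes the trial on an unadjusted comparison of two rates: "the test level α was set at 0.05", the type II "error probability β was set at 0.2", and "the required sample size of each group was calculated to be 177 cases by two-sided test". The Data collection section lists age, gender, APACHE II, SOFA and comorbidities among the patient characteristics, so the covariates will be to hand.

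**The concern.** The first two statements promise an adjusted analysis and name logistic regression for binary outcomes. The third names an unadjusted test for the one binary outcome that decides the trial. The section does not say how the two relate. The adjusted result could be read as the main result, as support or as a sensitivity analysis. Its covariates are given only as examples, and its methods only as possibilities.

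Two things are at stake. First, if the unadjusted and adjusted results fall on opposite sides of 0.05, the text does not settle which one carries the conclusion. Any choice made after seeing them raises the false-positive rate above the stated 5%. Blinding during the trial does not remove this freedom once allocation is revealed for analysis. Second, if the covariates predict pneumonia, an unadjusted primary test uses the data less efficiently than an adjusted one, and adjusting needs no new data.

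**Working it through.** **Inputs from the protocol.** Two-sided α 0.05 and β 0.2. For the rates, "the incidence of pneumonia within 48 hours after endotracheal intubation in the two groups was 16%(4/25) and 32%(8/25), respectively" (ceftriaxone, then control). Allocation 1:1, with 177 evaluable per group and 197 after 10% loss. The protocol gives no prognostic strength for any covariate, so every strength below is an assumption, shown as a range.

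**The plan's own figure.** With mean rate 0.24, the pooled two-proportion formula gives

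n = [1.960·√(2·0.24·0.76) + 0.842·√(0.16·0.84 + 0.32·0.68)]² / 0.16² = (1.184 + 0.499)² / 0.0256 ≈ 111 per group.

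The unpooled, arcsine and continuity-corrected versions give 108, 109 and 123. So 177 is not reproduced. The loss step is: 177/0.90 = 196.7, rounded up to 197. The mismatch is a separate matter. Here it means only that, at the stated rates, 177 per group already has high unadjusted power: z = (0.16·√177 − 1.184)/0.593 = 1.59, or about 94%.

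**Simulation with one fixed adjusted model.** There were 4,000 trials per setting. The unadjusted chi-square test was compared with a logistic regression on treatment, one prognostic score and three noise covariates. The assumed log odds ratio per SD of the score was 0, 0.5, 1.0 or 1.5. The null setting has 32% in both arms. All values are percentages; simulation error is about 0.3 points, since √(0.05·0.95/4000) = 0.0034.

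| Assumed log OR per SD | Null, 177 per arm: either test p<0.05 | Null: tests disagree | Power 32 v 16, 177 per arm: unadjusted / adjusted | Power 32 v 16, 109 per arm: unadjusted / adjusted |
|---|---|---|---|---|
| 0 | 5.0 | 0.6 | 95.0 / 94.6 | 80.7 / 79.4 |
| 0.5 | 5.8 | 2.5 | 94.6 / 95.1 | 79.1 / 80.3 |
| 1.0 | 6.5 | 3.4 | 94.3 / 96.7 | 81.1 / 84.8 |
| 1.5 | 7.2 | 5.0 | 94.6 / 98.2 | 80.3 / 89.1 |

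Each test alone holds its level: 4.6 to 4.9% unadjusted and 4.4 to 4.8% adjusted. The excess comes only from being able to use either. In the last row, 4.6 + 4.8 − 2.2 (both significant) = 7.2.

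**Other assumed models.** With two covariates at 0.4, 0.6 and 0.8 per SD, the either-test rate was 6.0%, 6.0% and 7.8%. With the four named covariates in one full model, at 0, 0.25, 0.4 and 0.6 (for sex, between the two categories), it was 5.0%, 6.3%, 6.9% and 8.0%. Across these models the range is about 5 to 8%.

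**If the covariate set is also chosen afterwards.** Allowing the chi-square test or any subset of the four named covariates gave 5.3%, 8.1%, 8.7% and 11.4% at the same strengths. This is the far end of what an open list permits.

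**Power for a smaller effect.** At an assumed 32% against 19.5%, with 177 per arm and two covariates at 0 to 0.8 per SD, adjustment gains about 0 to 8 points on an unadjusted power of roughly 77%. The 19.5% is not in the protocol; it illustrates a smaller effect.

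**Can the model be fitted?** Expected events are 0.24 × 354 ≈ 85. Treatment plus four covariates makes five terms, or 85/5 = 17 events per term.

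**The case against.** The strongest reply is that the section attaches exactly one test to the primary outcome, with a rule for chi-square against Fisher, and that the sample size was built on the same unadjusted comparison. That stands. A reader might infer two competing primary results, but the text does not say so. The natural reading is one unadjusted primary test plus an adjusted analysis of undefined status. No sentence allows success to be claimed on whichever result is significant, so the 5 to 8% describes what the wording fails to rule out, not a stated rule.

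A reader might also infer that adjustment as a whole depends on looking at the data. The text does not support this either: it states that factors will be adjusted for, and *if needed* may belong only to the stratified analysis. The covariates and method remain unfixed on either reading.

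It is also fair to say that an unadjusted test is valid in a randomised trial, and that the gain from adjustment rests on prognostic strengths the protocol does not give. With no prognostic value there is no gain.

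COPD is a further tempting argument. The Discussion criticises an earlier study in which "The incidence of chronic obstructive pulmonary disease in the control group was higher", while this trial keeps COPD patients and does not name COPD for adjustment. But that study was non-randomised, and the Discussion offers randomisation as the answer. Not naming COPD is no error.

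Finally, covariate lists are often left to an analysis plan, which is not shown here. That would excuse silence. This section is not silent: it promises adjustment and then describes it in terms that fix neither its content nor its role.

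**Conclusion.** The point holds as an ambiguity in stated text, together with a better method available at almost no cost. The primary test is valid, but the promised adjusted analysis of the same outcome has no defined role, an open covariate list and optional methods.

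If either the unadjusted test or one fixed adjusted model could be claimed, type I error would be about 5 to 8%. It could reach about 11% if the covariate subset were also chosen afterwards. Keeping the unadjusted test costs about 0 to 4 points of power at the protocol's rates and 177 per arm, and up to about 8 points at the assumed smaller effect. All these figures depend on assumed prognostic strengths; at zero strength, both the inflation from one fixed model and the power loss vanish. The plan should be changed, but the unadjusted test does not make the trial's result invalid.

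**What to change.** Before unblinding, state one primary analysis of the 48-hour outcome. The preferred form is a logistic regression on treatment and a fixed list of baseline covariates already collected, for example age, sex, APACHE II and SOFA, reported as a standardised risk difference with 95% CI. Delete *such as*, *may include* and *if needed*. Label the chi-square or Fisher test as supportive. Adding COPD to the list is optional.

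Keeping the chi-square or Fisher test as primary, with one fixed adjusted model labelled supportive, would also remove the ambiguity, but it forgoes the possible gain in power.

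The cost is a few sentences and no new data. The standardised risk difference may need a short script outside SPSS. Which patients enter the analysis is a separate issue that this change does not settle.

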### Inclusion and exclusion criteria

Patients with ICH undergoing endotracheal intubation in Dong E Hospital of Shandong Province from April 2023 to April 2024 will be included. Inclusion criteria are: (1) age > 18 years; (2) ICH due to various causes; (3) endotracheal intubation; and (4) subjects understood and signed the informed consent. The following patients will be excluded from this study: (1) pneumonia occurred before endotracheal intubation; (2) aspiration occurred before endotracheal intubation (e.g., aspiration that is considered possible clinically, such as epilepsy; prehospital vomiting; vomit on the patient’s clothing; or vomit visible in the oropharynx at the beginning of intubation attempts); (3) received antibiotics before endotracheal intubation; (4) received other antibiotics within 48 hours after enrollment (especially before diagnosis of aspiration pneumonia); (5) patients who died within 48 hours after endotracheal intubation without aspiration pneumonia; (6) allergic history to cephalosporin antibiotics; and (7) drinking history within one week before endotracheal intubation, as the use of cephalosporin after drinking alcohol can cause a disulfiram reaction. Of note, patients with COPD will not be excluded from the study. Schedule of enrolment, interventions, and assessments are shown in **Fig 1**. A simplified schematic of the trial design is shown in **Fig 2**.

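### The ventilation outcome that is tested is not the one declared, and the raw durations carry no rule for deaths, so an arm with more deaths can look better

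*Protocol article*

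**What the plan says.** The Research outcomes section, like the Abstract, lists the secondary outcomes as "intensity of antimicrobial use, length of hospital stay, duration without mechanical ventilation, and 28-day mortality". The ventilation outcome there is time spent off the ventilator. It is given no definition, no time window and no value for a patient who dies.

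The Statistical analysis section, when it turns to the secondary outcomes, names "continuous variables like length of ICU stay, duration of mechanical ventilation, and hospital length of stay". The ventilation variable is now time spent on the ventilator. Length of ICU stay also appears, although it is only an item in the data collection list and not a declared outcome. The tests are fixed: "Differences between the groups will be tested using independent t-tests for normally distributed data or Mann-Whitney U tests for non-normally distributed data".

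For time-to-event outcomes, "such as the time until the development of aspiration pneumonia or extubation, Kaplan-Meier survival analysis will be used", with a log-rank test. No censoring rule is stated.

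Death enters in two other places only. It is a separate binary outcome ("Categorical outcomes such as 28-day mortality will be analyzed using chi-square" or Fisher's exact test), and one exclusion criterion removes "patients who died within 48 hours after endotracheal intubation without aspiration pneumonia". Later deaths stay in the analysis. The missing-data rule ("Missing data will be handled using a complete case analysis, where possible", with multiple imputation if much is missing) does not mention death.

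**The concern.** There are two linked problems.

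**The declared outcome is not the analysed one.** Time on and time off the ventilator are not mirror images once patients die. For a patient who dies ventilated on day 3, time on the ventilator is 3 days and looks good. Days alive and off the ventilator are 0, the worst possible value. Followed as written, the plan leaves a declared secondary outcome without an analysis and tests a different quantity.

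**The stated tests ignore death.** Death ends both a hospital stay and a ventilation episode. In a t-test or Mann-Whitney test on raw durations it lowers the value and so counts in the arm's favour. If mortality differs, the comparison can favour the arm with more deaths. Separately, if deaths are censored in a Kaplan-Meier analysis of extubation, the curve estimates what would happen if nobody died and overstates the proportion actually extubated.

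**Working it through.** The plan gives no figure to reproduce on this point, and no mortality, stay or ventilation data. Every clinical input below is an assumption. The only documented inputs are the group sizes in the Sample size calculation section: 177 per arm, and 177/0.90 = 197 after allowing for 10% loss.

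**1. Outcome mismatch (no arithmetic)**

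| | Ventilation outcome | Hospital stay | ICU stay |
|---|---|---|---|
| Research outcomes | time off ventilator | yes | not listed |
| Statistical analysis | time on ventilator | yes | tested |

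**2. Raw ventilation duration**

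Assume the underlying time to extubation T is exponential with mean 12 days in both arms, and that deaths fall uniformly on days 2 to 10.

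- If death occurs at day u, mean ventilation is E[min(T,u)] = 12(1 − e^(−u/12)).
- Averaged over u from 2 to 10: 12 − (144/8)(e^(−2/12) − e^(−10/12)) = 12 − 18(0.8465 − 0.4346) = 4.59 days.
- 40% mortality: 0.60 × 12 + 0.40 × 4.59 = 9.03 days.
- 30% mortality: 0.70 × 12 + 0.30 × 4.59 = 9.78 days.
- Difference: about 0.74 day in favour of the arm with more deaths. Simulations gave 0.75 to 0.79.

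Simulated Mann-Whitney rejection at two-sided 0.05:

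| Mortality | n per arm | Rejection |
|---|---|---|
| 40% vs 30% | 197 | about 11% |
| 40% vs 30% | 177 | about 9% |
| 35% vs 30% | 197 | about 6% |
| equal | 197 | about 5% |

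**3. The same patients scored as days alive and ventilator-free to day 28**

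- A survivor's mean is 28 − 12(1 − e^(−28/12)) = 28 − 10.84 = 17.16 days. A death scores 0.
- 40% mortality: 0.60 × 17.16 = 10.30. 30% mortality: 0.70 × 17.16 = 12.01.
- The arm with more deaths is now worse by about 1.7 days.

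**4. Sensitivity to the model**

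Alternatively, assume constant hazards with extubation at 0.07/day in both arms, n = 177, and death at 0.03 against 0.05/day. Then 28% against 40% die on the ventilator by day 28. The median raw duration falls from 6.9 to 5.8 days, and the false advantage is significant in about 32% of trials. Mean ventilator-free days (death = 0) fall from 13.0 to 11.6. The contrast is larger here: 12 points of deaths on the ventilator. In step 2 only 1 − 4.59/12 = 62% of deaths occur before extubation, so a 10-point mortality difference is about 6 points of deaths on the ventilator.

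**5. Kaplan-Meier for extubation, if deaths are censored**

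With constant daily hazards e (extubation) and d (death), 1 − KM(28) = 1 − exp(−28e). The true cumulative incidence is e/(e+d) × [1 − exp(−28(e+d))].

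| e | d | 1 − KM at day 28 | Truly extubated | Dead |
|---|---|---|---|---|
| 0.05 | 0.03 | 75.3% | 55.8% | 33.5% |
| 0.06 | 0.02 | 81.4% | 67.0% | 22.3% |

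**6. Log-rank**

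With equal extubation hazards (0.05/day), death at 0.03 against 0.05/day and 177 per arm, log-rank with deaths censored rejected in 5.3% of 1,500 simulated trials. With deaths kept in the risk set to day 28 it rejected in about 30 to 33%.

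**The case against.** The strongest reply has four parts.

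- **Censoring and death rules often sit in a full protocol or SAP, which is not shown, and the analysis section gives examples rather than a closed list.** This stands for the Kaplan-Meier point: no censoring rule is stated, so that point is conditional. It does not remove the conflict between two stated sections, and the tests for the raw durations are named.
- **The size rests on assumptions.** This stands. A 10-point mortality difference from one antibiotic dose is large. The single-dose study that the Discussion describes in ventilated comatose patients found no effect on mortality. With equal mortality there is no inflation.
- **Log-rank with deaths censored is a valid comparison.** This stands. A reader might infer that the test mixes extubation with death; it does not, since it compares extubation hazards (step 6). Keeping deaths in the risk set, or using Gray's test, asks a different question and is a choice of estimand. A reader might also infer that Kaplan-Meier would favour the arm with more deaths. With equal hazards and independent censoring the curves coincide and only the shortfall in extubations is hidden. A reversal needs informative censoring, for example deaths concentrated in patients slow to extubate, and the protocol gives no data on that.
- **These are secondary outcomes, and 28-day mortality is compared separately.** This stands as a limit on consequence. Seeing an imbalance in deaths does not correct the duration tests.

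It might also seem that time to pneumonia needs the same treatment. Within the 48-hour window it does not, because the exclusion criteria remove deaths in that period without pneumonia.

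**Conclusion.** The point holds for the secondary outcomes and should be corrected; the primary comparison is not affected. The mismatch between the declared and the tested ventilation outcome is certain from the text, as is the absence of any rule for deaths in the durations. The direction of the distortion is also clear: death shortens a raw duration.

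Its size is not known from the documents. Under 40% against 30% mortality and an identical ventilation course, it is about 0.7 to 0.8 day and 9 to 11% rejection instead of 5%. It is larger if deaths on the ventilator differ more, and essentially nil if mortality is equal or differs by 5 points. For extubation, the supported criticism is overstatement of the proportion extubated if deaths are censored (for example 75% against a true 56% with 34% dying), not an invalid log-rank test or a reversed comparison.

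**What to change.** Amend the Statistical analysis section as follows.

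- Analyse the declared ventilation outcome as days alive and free of mechanical ventilation to day 28, with deaths by day 28 set to 0, by Mann-Whitney. Show mortality and ventilation duration in survivors alongside. Put the same definition in Research outcomes.
- Report hospital stay as time to discharge alive, with death as a competing event.
- Describe extubation by cumulative incidence with death as a competing event. If log-rank with deaths censored is kept, label it a comparison of extubation hazards.
- Give raw ventilation, hospital and ICU durations descriptively only, by survival status, and mark ICU stay as additional to the declared outcomes.

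The cost is wording and recoding. Ventilation duration, length of stay and 28-day survival are already in the data collection list. With complete follow-up to day 28, holding deaths in the risk set until day 28 makes one minus Kaplan-Meier equal the cumulative incidence, so SPSS 20.0 can produce the curves. The small downside is that the composite combines mortality and duration, so its components must always be shown with it.
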